***Primary outcome (Participants)***						
General psychological distress	*General Health Questionnaire (GHQ-12)*	Participants measure their general psychological distress		X	X	X
***Secondary outcomes (participants)***						
Depression symptoms	*Depression symptoms (PHQ)*	Participants rate depression symptoms over past two weeks		X	X	X
Daily functioning	*WHODAS*	Participants rate their ability to engage in daily activities		X	X	X
Post-traumatic stress symptoms	*PTSD Checklist for DSM5 (PCL-5)*	Participants rate their post-traumatic stress symptoms on a scale		X	X	X
Perceived social support	*Multidimensional Scale of Perceived Social Support (MSPSS)*	Participants assess their own connectedness with close family, friends and other forms of support		X	X	X
Somatic symptoms	*Somatic Symptom Scale-8 (SSS-8)*	Participants rate how much they have been bothered by somatic symptoms		X	X	X
General psychological distress	*Heart-mind*	Participants note if they have had any *“man ko samasya”* or heart-mind problems recently			X	X
**Additional measures of mechanisms and potential moderators**						
Ways of coping	*Reducing Tension Checklist (RTC)*	Participants assess their own behavioral and psychosocial skills related to coping		X	X	X
Traumatic events	*Traumatic Events Inventory (TEI)*	Participants rate if they have been exposed to certain traumatic events throughout their lifetime		X		X

**Table 3 Tab3:**
[figure not shown]
Schedule of enrollment, interventions, and assessments for Group PM+

The WHO Disability Assessment Scale (WHODAS) is a generic instrument assessing health and disability in adults. It assesses difficulties that people are experiencing during the last 30 days, due to their illness, across six domains of functioning (cognition, mobility, self-care, getting along, life activities, and participation). Difficulties are scored on a five-point Likert scale of: not at all difficult, a little difficult, sometimes difficult, very difficult, or always difficult. The WHODAS can be used with all diseases and across cultures. The scale has been previously used in Nepal and has a good internal consistency between items (α = 0.90) and validity with multiple mental health measures for depression (*r* = 0.616, *p* < 0.001), anxiety (*r* = 0.624, *p* < 0.001), and PTSD (*r* = 0.499, *p* < 0.001) [4, 44].

The Patient Health Questionnaire (PHQ-9) is a ten-item instrument measuring symptom depression [40]. It has been translated and clinically validated in a primary care population in Chitwan, Nepal: the validated cut-off score of ≥ 10 (sensitivity = 0.94, specificity = 0.80, PPV = 0.42, NPV = 0.99, positive likelihood ratio = 4.62, and negative likelihood ratio = 0.07) [30].

The original Post-traumatic stress disorder Check List (PCL)-5 is a 20-item checklist corresponding with the 20 DSM IV PTSD symptoms. To diminish the burden of questionnaires administered by participants in this study, the eight-item version will be used. This was shown in a recent study to have comparable diagnostic utility to the 20-item PCL-5 [45] and has been used in Nepal and will be used in this study to diminish the burden of questionnaires administered by participants [46].

The Multidimensional Scale of Perceived Social Support (MSPSS) [42] is a self-rating tool of perceived social support from three categories of support: family, friends, and significant other. It has been locally adapted [47] and validated to use in Nepal [48]. The MSPSS consists of 12 questions that are rated on a five-point Likert scale ranging from 1 (“very strongly disagree”) to 5 (“very strongly agree”). Higher scores indicate higher perceived levels of social support.

The Somatic Symptom Scale (SSS) is an eight-item patient-reported outcome measure of somatic symptom burden [43] that has been translated and adapted using a standard cross-cultural approach [49].

#### Other measures and further data

Competency and fidelity will be assessed with a modified version of the Enhancing Assessment of Common Therapeutic Factors (ENACT) tool tailored for Group PM+ [50]. The ENACT scale is an 18-item assessment for common factors in psychological treatments that can be used by non-specialists in different settings.

Demographic characteristics of participants will be recorded at baseline, including age, years of education, occupation, and living situation. Traumatic events will also be assessed with the Traumatic Events Inventory (TEI), an 11-item assessment of traumatic exposure associated with poor mental health outcomes [51]. The TEI has previously been used in Nepal [52] . A natural disaster questionnaire has also been developed for this trial. This consists of five questions on whether participants were affected by floods, earthquakes, landslides, fires, or other natural disasters in the last 5 years. Participants will be asked if their property was damaged and if they themselves or any relatives and friends were hurt by such natural disasters. Behavioral and psychosocial skills related to coping with emotional distress will be assessed with the Reducing Tension Checklist, which contains a 12-item assessment of behavioral and psychological skills to evaluate skill acquisition of PM+ skills with one free response question based on the PSYCHLOPS [51, 52]. It has been adapted based on PM+ content and findings in phase 1 of the project [28].

During PM+ sessions the Subjective Units of Distress Scale (SUDS) will be used. The SUDS, a scale of 0 to 10 for measuring the subjective intensity of disturbance or distress currently experienced by an individual [53], will be used for each participant during the second to fifth PM+ sessions. The scale has been previously used in Nepal [54].

### Masking

In this project, research assistants administering all interviews, community informants, research supervisors, and study statisticians will be blinded. The intervention does not allow for the intervention facilitators and participants to be blind to treatment allocation. Blinding of assessors will be ensured by minimizing the chance of contact between assessors and facilitators and having two separate offices for the research and clinical staff. Assessors will also prompt participants not to share any information on the type of treatment that they receive and explain that they are not supposed to know. After each assessment, assessors will be asked to indicate what treatment they think each participant will or has received (e.g., medication, one-on-one counseling, group counseling, referral, etc.). This will provide some data on the amount of unblinding that might occur in the RCT. Furthermore, each of the research assistants sign a contract in which they agree to not share any details of the study with others.

Given the challenges of blinding in c-RCTs and the concerns about the potential for selection bias given that participant recruitment occurs after randomization of the wards in which the participants reside [55], we have used the “timeline cluster” to visualize procedures in relation to blinding and participant recruitment [56]. Specifically, we generated Fig. 2 using an online open-access tool developed by the “timeline cluster” authors [56]. This figure provides additional details to complement the overall study flow chart (Fig. 1), including information on whether a specific stage of the process pertains to clusters, to participants, or to both. The dark boxes indicate stages in the procedure when both participants, and the study personnel who will interact with those participants, will be blinded to which arm the cluster has been allocated to. We will use a design so that study participants are recruited by trained RAs who do not know which arm the ward (cluster) has been assigned to (see up to stage 7 in each arm, Fig. 2). During service delivery (stages 8–9a in Group PM+ and stage 9b in EUC), participants cannot be blinded to study arm. As noted above, however, we have designed the midline and endline data collection procedures so as to try to ensure that the RAs conducting the interviews are blinded to study arm (stages 10–11 in both arms), which is indicated by the light grey shading (i.e., indicating partial blinding because the participants are no longer blinded at this stage). Importantly, when commencing the interview, the RA will emphasize to the participants how important it is that the participants do not reveal details about what kind of services they have received. We recognize that, within a specific ward, if an RA is inadvertently unblinded while conducting the interview with a participant before the final interview in that ward (i.e., before interviewing the eighth of the eight enrolled participants), that RA would therefore be unblinded for the interviews of remaining participants. We will record data as to whether such unblinding occurred and therefore will be able to report on any threats to data validity. And, even in such a case, the RAs receive rigorous and comprehensive training on procedures to objectively record responses to our instruments and measures and, therefore, we expect to be able to mitigate any potential for measurement bias that could arise as a result of unblinding.

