Restricted randomization will be used. Specifically, we will first use stratification by “ward gender” (i.e., randomization separately within 14 “male” wards and within 58 “female” wards). Then, within each “ward gender”, we will use covariate constrained randomization to account for three baseline cluster-level covariates that are expected to be related to participant outcomes and for which it is important for us to achieve balance between the two study arms. Those three covariates, all defined as binary, are: (1) access to mental health services (high or less than 1 h to reach nearest PHCC vs. low or less than 1 h to reach nearest PHCC); (2) disaster risk (high or landslides or flooding in the last 3 years vs. low-to-moderate or minimal landslides or flooding in the last 3 years); and (3) rural/urban status (rural defined as wards that do not touch a major highway, majority of homes made of wood/straw/mud, and no local markets and urban defined as wards close to highways, majority of homes made of concrete and access to local markets). Covariate constrained randomization is a generalized form of stratification which can be used to simultaneously balance on multiple baseline covariates without the need to formally define strata based on the cross-classification of those covariates [25]. In practice, in order to perform covariate-constrained randomization within the two strata defined by the 14 “male” wards and the 58 “female” wards, we will separately implement covariate constrained randomization in Stata software (version 14 [26]) using the *cvcrand* procedure [27]. Randomization will be performed in advance of enrolment of participants and will be conducted by the study statistician who does not know the study region. The statistician will use a simple data set with only the ward codes and three relevant covariates to ensure that there is no room for bias in the implementation. Moreover, a seed will be set so that the implementation is reproducible in Stata statistical software.

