### Procedures

Each ward of participating municipalities in Morang district will have one community informant (CI) who will conduct recruitment through the use of the Community Informant Detection Tool (CIDT) and community sensitization activities. CIs are often Female Community Health Volunteers (FCHVs), mothers’ group members, or social mobilizers within their respective communities. CIs will, as much as possible, also be gender-matched for the “gender” of their wards. CIs from intervention and control wards will be trained separately to maintain blinding. Control ward CIs will not be given any information on Group PM+ or any other information about the existence of an intervention arm. Intervention CIs will additionally be given a 1-day training to become Group PM+ ‘helpers’ for the sessions.

The CIs will be trained on the CIDT to identity people with common mental disorders in the community. The CIDT is a pro-active case detection approach aimed to increase help seeking using a vignette-based tool designed for the ease of use by lay people. It has been developed and tested in Nepal [35], with positive results on the positive predictive value (0.68) and increasing the utilization of mental health services [36]. A general distress CIDT version had been adapted for this trial [28], which includes gender-matched vignettes for the “gender” of the wards.

After the community informant identifies a person in the community who matches the symptoms described in the vignettes, they will be asked if they would like support for their problems. If so, the research assistant (RA) will then conduct the consent and screening procedures.

People who are identified as meeting the exclusion criteria initially by the RAs will be referred to health workers trained in mhGAP, hospitals with psychiatric services, or counselors. People that meet the inclusion criteria for the study, in both the intervention and control wards, will receive a visit from the CI for a family meeting. Based on the preference of the participants, this can either be with or without their family. After the family meeting, RAs will conduct the baseline assessment with enrolled participants. Once baseline is completed, only those in the intervention group will be contacted by CPSWs to inform them about Group PM+. After all participants in an intervention ward have been contacted by the CPSW, Group PM+ sessions will start.

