### Informed consent

The consent procedures consist of two steps, first informed consent for screening and then informed consent for participation in the Group PM+ trial [10] . After identification by the CI, potential eligible people will be approached by the research assistant for informed consent for screening. If a participant screens positive, the CI will give more information about the research project and will conduct the full trial informed consent during the family meeting.

All respondents who decide to participate will provide written consent, if possible. Full information on the study will be provided in local, lay Nepali language before obtaining consent from each participant. Given high rates of illiteracy, the consent form will be read to all participants. After providing verbal consent, literate participants will be asked to acknowledge the process with a signature. For illiterate participants, verbal consent or adding a symbol or sign will be sufficient. We will make sure that potential participants fully understand what participation entails and that they, at any time and without any consequences, can withdraw their consent without having to give an explanation.. Participants will be made aware that refusal to participate will not have an impact on any type of support they receive outside the study. For the qualitative interviews, separate written informed consent will be taken at the time of the interview.

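### Community informants are described as blinded, but those in intervention wards are trained as Group PM+ helpers, and they help decide who enters the trial after wards are randomised

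*Protocol article*

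**What the plan says.** All references are to the protocol article.

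- **Order.** Under Randomization: "Randomization will be performed in advance of enrolment of participants".
- **Blinding claim.** Under Masking: "research assistants administering all interviews, community informants, research supervisors, and study statisticians will be blinded". No limit by arm or by time is given.
- **Case-finding.** Under Procedures, each ward has "one community informant (CI) who will conduct recruitment through the use of the Community Informant Detection Tool (CIDT") together with community sensitization.
- **Consent.** Under Informed consent, once a person screens positive "the CI will give more information about the research project and will conduct the full trial informed consent during the family meeting". Procedures places that meeting before the baseline assessment.
- **Knowledge by arm.** Procedures has the two sets of CIs trained separately. "Control ward CIs will not be given any information on Group PM+ or any other information about the existence of an intervention arm". By contrast, "Intervention CIs will additionally be given a 1-day training to become Group PM"+ helpers. The Group PM+ intervention section adds that helpers take part in practice groups with the facilitators, remind participants of sessions and provide child care.
- **The stated safeguard.** Masking acknowledges "concerns about the potential for selection bias given that participant recruitment occurs after randomization of the wards in which the participants reside" and answers with a design in which "study participants are recruited by trained RAs who do not know which arm the ward (cluster) has been assigned to". The CI's part in finding and consenting people is not discussed there.

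**The concern.** In a cluster trial that enrols after randomisation, random allocation of wards does not by itself make the enrolled participants comparable. That depends on whether those who decide whom to approach, and how the trial is presented to them, act alike in both arms. Here one CI per ward does both, for a target of eight participants.

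A CI who knows that the ward will host a group, and who will help run it, may put forward or encourage people thought suited to a group. A control-ward CI has no such prompt. The difference could lie in motivation, sociability or expectation, which the baseline GHQ-12 captures only in part. Such a bias does not shrink as wards are added, and it cannot be repaired once enrolment has finished.

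There is also a plain reporting problem: a blinding claim would be published that the same article contradicts.

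**Working it through.** **1. The masking statement against the other sections**

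| Step | Who does it | What that person may know |
|---|---|---|
| Find candidates with the detection tool (Procedures) | CI | Intervention CI: trained as helper at an unstated date. Control CI: told of no intervention arm |
| Consent for screening, then screening (Procedures; Informed consent) | RA | Blinded (Masking) |
| Trial information and full trial consent at the family meeting (Informed consent) | CI | As in row 1 |
| Baseline assessment (Procedures) | RA | Blinded |

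A helper at Group PM+ sessions knows that the ward receives Group PM+. The unlimited blinding claim is therefore wrong for the CIs of the 36 intervention wards at some point in the trial, whatever the training date. The safeguard in Masking covers rows 2 and 4 and leaves out rows 1 and 3.

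**2. Is the helper training before enrolment?** The text gives no date. Four things point that way:

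- CIs are trained separately by arm, to maintain blinding.
- Helpers join practice groups. The facilitators' practice rounds come before 12 of the 15 are selected, so before the trial groups.
- Midline is at week 7, about 1 week after the intervention ends (Design and setting), so the last session falls at about week 6. If the five sessions are weekly (my assumption), session 1 falls about 6 − 4 = 2 weeks after baseline or a little earlier.
- Recruitment opened on 25 November 2018, with completion likely by 31 May 2019 (Trial status): 187 days, or 26.7 weeks. Less 20 weeks of follow-up, that leaves about 6.7 weeks to enrol all wards.

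This makes early training likely. It does not establish it.

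**3. The plan's own figure.** Inputs from Sample size justification: 72 wards (36 per arm), 6 analysed per ward after up to two of eight drop out, ICC 0.2, SD 7, effect size 0.46, two-sided 5%.

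- Design effect = 1 + (6 − 1) × 0.2 = 2.0
- Per arm: 36 × 6 = 216; effective 216 / 2.0 = 108
- Power = 0.922 (normal) or 0.915 (t, 70 df), against the stated 90% or more

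The power statement reproduces and is not in dispute.

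**4. What a residual shift would do.** SE of the arm difference = 7 × √(2 × 2.0 / 216) = 0.953 points. For a shift b that adjustment does not remove, the two-sided type I error is 1 − Φ(1.96 − b/SE) + Φ(−1.96 − b/SE).

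| Assumed shift b (points) | In SD (b/7) | Share of the 3.2-point target | Type I error |
|---|---|---|---|
| 0 | 0 | 0% | 5.0% |
| 0.25 | 0.04 | 8% | 5.8% |
| 0.5 | 0.07 | 16% | 8.2% |
| 0.7 | 0.10 | 22% | 11.4% |
| 1.0 | 0.14 | 31% | 18.3% |
| 1.4 | 0.20 | 44% | 31.2% |

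Every value of b is an assumption. The documents give neither a size nor a direction.

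**The case against.** The other side has several good points.

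- **Timing.** No sentence says that CIs learn their arm before recruitment. Masking says that the dark stages of Fig. 2 are those at which participants and the personnel dealing with them are blinded, and it places blinded recruitment up to stage 7. CIs deal with participants. Fig. 2 was not available for this review and may show the order. This stands, and it is why early training is put here as an inference only.
- **Both arms.** A reader might infer that CIs in general know their allocation. The text does not support that: control-ward CIs are deliberately kept unaware. The problem is unequal knowledge between arms.
- **Safeguards.** A blinded RA takes screening consent and screens with fixed instruments (Participants). Case-finding uses a vignette tool. The family meeting has the same format in both arms (Enhanced usual care), so taking baseline after it is not in itself an arm difference. Facilitators contact intervention participants only after baseline. The model adjusts for the baseline outcome, and supportive analyses adjust for imbalanced covariates (Statistical analyses). These limit the likely bias. They do not reach unmeasured differences among people whom the CI chose to refer and who then agreed.
- **Consent content.** A reader might also infer that a control-ward CI cannot give the full study information that Informed consent promises. A consent form is read to every participant and is not shown, so this is unproven.
- **Size.** The table in step 4 is correct arithmetic on assumed inputs, and small shifts do little harm.

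**Conclusion.** The concern holds in a limited form. The statement that CIs are blinded is wrong as written for intervention wards. CIs whose knowledge can differ by arm identify candidates and take full trial consent after randomisation, and the safeguard offered against selection bias covers only the RAs. That much follows from the text.

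Whether the unequal knowledge exists at the moment of recruitment depends on the undated helper training. It is likely, given the separate training, the practice groups and the short interval before session 1, but it is not stated.

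The amount of bias is unknown. The range of about 6% to 31% for type I error rests wholly on an assumed residual shift of 0.25 to 1.4 points, with the plan's own SD, ICC and ward numbers. It should not be read as an estimate of this trial's error rate. The sample size calculation is unaffected.

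**What to change.** 1. **Correct the text.** Amend Masking so that intervention-ward CIs are not described as blinded, and say how the selection-bias argument applies to their steps. Reconcile it with Procedures, Informed consent and the helper paragraph of the Group PM+ intervention section. State when helper training takes place relative to enrolment.
2. **Wards not yet recruited.** Hold helper training and any disclosure of arm until the ward's baseline interviews are complete, where the schedule allows. Have the blinded RA, who already visits each candidate, take full trial consent with one arm-neutral script. Baseline need not move ahead of the family meeting.
3. **Report.** Give numbers identified, screened, eligible and consenting per ward, by arm. Where helper training came before enrolment, report the intervention-ward CIs as unblinded.

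**Cost.** An ethics notification, some added RA time and possibly a short delay before session 1. Because midline is fixed at 7 weeks after baseline and practice takes place in an adjoining district, there is limited room to defer practice groups, and deferral may not be feasible everywhere. Recruitment has been open since 25 November 2018, so item 2 helps only the remaining wards. Items 1 and 3 apply to all.
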